### Material and variables

#### Baseline cognitive assessment.

Neuropsychological assessment is used to determine participants’ cognitive functioning. This evaluation takes place at the beginning of the study (Fig 2).

**Fig 2 pone.0341744.g002:**
[figure not shown]
Study procedure.

The presence of cognitive impairment associated with dementia is assessed using the Spanish version of the Addenbrooke’s Cognitive Examination-Revised (ACE-R) [17]. The ACE-R is a cognitive screening tool that evaluates five domains. The total score is 100 points, distributed across the following cognitive domains: attention/orientation (18 points), memory (26 points), verbal fluency (14 points), language (26 points) and visuospatial skills (16 points). Higher scores on the ACE-R indicate better cognitive performance. This tool has proven sensitive in detecting cognitive dysfunction in older adults with dementia. Cognitive status is also evaluated using the Mini Mental State Examination (MMSE) [18]. The ACE-R incorporates the MMSE, so an MMSE score can be obtained through administration of the ACE-R. The MMSE totals 30 points, with higher scores indicating better cognitive functioning.

Verbal learning and memory are assessed using the Spanish Verbal Learning Test (TAVEC) [19]. This task involves learning a list of words presented to the participant as though it were a shopping list. The list comprises 16 words from four different semantic categories. Five learning trials are conducted with this list (List A), followed by an interference trial with a new list (List B). List B shares the same format as List A, with 16 words drawn from four categories; two of which overlap with List A and two of which are different. This is followed by short-term free recall of List A and a cued short-term recall, where participants are given the semantic categories as prompts. After a 20-minute interval, a long-term free recall test is administered, followed by a cued long-term recall and, finally, and a recognition test. Participant performance is analysed according to the standardised norms for this test.

Cognitive function in daily life is assessed using the Spanish version of the Everyday Cognition Scale (ECog), which has been adapted and validated for older Spanish-speaking adults [20]. Designed for older adults, this scale evaluates daily functioning in the cognitive domains of memory, planning, language organisation, divided attention and visuospatial and perceptual skills. Each domain consists of several questions, and responses are made in comparison to performance on the same tasks 10 years earlier. Response options are: ‘1 = no change, the same or better’, ‘2 = sometimes worse than before, but not always’, ‘3 = usually a bit worse than before’, ‘4 = always worse than before’. Participants may also respond ‘Don’t know or not applicable’. An average score is calculated for each domain, along with a total scale score.

Symptoms of depression are assessed using the shortened Spanish version of the Geriatric Depression Scale by Yesavage (GDS) [21]. This version includes 15 yes/no questions and is specifically designed for older adults. A cut-off score of 5 on the short version is used to indicate the presence of depression.

Visual-motor coordination, visual scanning and alternating attention are assessed using a Spanish-language version of the Trail Making Test, for which equivalence with English versions has been established in Spanish-speaking samples [22], which has two parts. In Part A, the participant is asked to connect 25 randomly distributed numbers on a page in ascending order as quickly as possible. In Part B, the participant must connect 25 numbers and letters in alternating order. The time taken to complete each part and the number of errors made are recorded. Significant time differences in task completion and errors made between both versions, suggest switching and alternating attention problems.

Visuoconstructive abilities and visual memory are assessed using the Rey-Osterrieth Complex Figure Test, applying normative data derived from monolingual Spanish-speaking older adults [23]. This test consists of three phases. In the first, the participant is asked to copy a complex figure. Immediately afterwards, the model is removed, and the participant is asked to reproduce it from memory. A delayed recall is then administered after 20 minutes. This allows for assessment of both immediate and delayed visual recall.

Language is evaluated using the Verbal Fluency Test (TFV) [24], which includes phonological and semantic fluency tasks. Participants are asked to produce as many words as possible in one minute for each of the following phonetic categories: words beginning with F, A and S. For semantic fluency, they are asked to name items from the categories: animals, fruits, items of clothing and kitchen utensils. Both correct answers and mistakes are analysed.

Executive functions, specifically planning ability, are assessed using the Zoo Map Test [25]. This test has two versions, Version 1 and Version 2. In Version 1, participants are asked to plan a route to visit specific locations on a zoo map, following a set of rules (e.g., where to start or finish, or which paths may be used only once). In Version 2, participants perform the same task with the same Version 1 rules, but this time are guided step by step. Planning time, execution time and number of mistakes are analysed in this task.

The battery follows a fixed administration order to avoid interference effects and respect normative protocols: (1) ACE-R, (2) TAVEC, (3) ECog, (4) GDS (during TAVEC 20-min delay if needed), (5) TMT A/B, (6) Rey Complex Figure Test (20-min delay between copy/immediate and delayed recall, during which Verbal Fluency Test may be completed if pending), (7) Zoo Map Test. Estimated total duration: 90–120 minutes, varying by participant performance and including breaks as needed.

To mitigate fatigue in older adults, breaks are offered whenever requested by the participant or observed by the examiner (reduced alertness, motor slowing). If excessive fatigue prevents completion, the session is paused or rescheduled within 1 week maximum.

#### Baseline physical assessment.

Physical assessment provides insight into the physical condition of the participants.

Frailty is assessed using the Short Physical Performance Battery (SPPB) whose validity, reliability and reference values have been established in older spanish adults [26]. The SPPB consists of three components that assess balance, gait speed and the ability to stand up from and sit down on a chair five times. Each component is scored out of 4 points, based on the time taken by the participant to complete each task. A total score of less than 10 is considered indicative of a high likelihood of frailty [27].

Balance is evaluated using the Spanish version of the Mini Balance Evaluation Systems Test (Mini-BESTest), which has shown good psychometric properties in community-dwelling older adults [28]. This test includes 14 items that assess anticipatory postural adjustments, postural responses, sensory orientation and dynamic gait stability. Each item is rated on a scale from 0 to 2. Lower scores indicate greater balance impairment [28]. Additionally, the Mini-BESTest includes the Timed Up and Go Test (TUG), conducted both with and without a dual task. The TUG [29] measures the time it takes for the participant to rise from a chair, walk three metres, turn around, return to the chair and sit down again. Three trials are conducted, and times exceeding 12 seconds are interpreted as indicative of high frailty risk [27]. In the dual-task TUG, participants are also asked to count backwards in threes from a specified number before and during the task. A reduction in walking speed of more than 10% between the single and dual-task TUG, or stopping either the walking or the counting, indicates increased frailty. Balance is also assessed using the Functional Reach Test (FRT), for which a Spanish version has demonstrated good validity and reproducibility in older adults [30]. This test measures how far a person can reach forward while maintaining their balance without moving their base of support. Greater reach distances indicate a lower risk of falls.

All these tests are performed at the beginning of the study. In addition, the TUG and FRT are repeated after the intervention (Fig 2).

#### Outcome measurements.

The primary outcome measures are:

Changes in muscle activity [31], monitored through surface electromyography (EMG). EMG signals are recorded using Delsys Trigno system devices (Delsys Inc., Boston, USA), offline mode, 1259 Hz sampling bilaterally on the biceps brachii, multifidus, gluteus medius, biceps femoris, medial gastrocnemius, vastus lateralis and tibialis anterior. Electrodes are placed following SENIAM guidelines [32]. After placement and prior to the experimental session, two maximum voluntary contractions (MVCs) are performed for each muscle, with a six-second rest in between. These MVCs are used for data normalisation in subsequent analyses. Time-based EMG outcome measures include the root mean square (RMS), synchronisation of activation between muscle groups, and the ratio of activation between muscles. Frequency-based measures include the median frequency (MDF). EMG data are collected only during motor task testing, both at baseline (t_1_) and during the experimental test (t_2_) for all participants. No EMG recording occurs during baseline physical assessments (SPPB, Mini-BESTest/TUG, FRT), which characterize participant frailty prior to stress exposure (Fig 2).Ground pressure is measured using a custom-made Fitness MAT DEV KIT 1.9 mat (80 × 80 cm) developed for this project (Sensing Tex S.L., Sant Cugat del Vallès, Spain). This mat includes pressure sensors that provide precise information on weight distribution and participant behaviour during weight-shifting tasks [33]. The mat features a sensing area of 160 × 56 cm and a matrix of 2,240 sensors with a spatial resolution of 20 mm between sensors (80 × 28 matrix), local pressure mapping. Each pressure sensor has a measurement range of 20–10,000 mmHg, with 10% accuracy and a linearity coefficient of 0.99. Data are collected using a 12-bit resolution electronic unit with Bluetooth and USB connectivity. Pressure data are recorded during motor task tests at both baseline (t_1_) and the experimental test (t_2_).Acceleration and deceleration during object manipulation are measured using WT9011DCL devices (WitMotion ShenZhen Co. Ltd., ShenZhen, China). These triaxial IMUs are attached to the bottles participants must handle during fine motor task tests. Data are recorded during both baseline (t_1_) and experimental (t_2_) sessions for all participants.Balance, additionally assessed using the TUG and FRT before and after the experimental session.

Secondary outcome measures include: heart rate variability (HRV), respiratory rate (RR) and a visual analogue scale (VAS) assessing the sensation of unease, restlessness or discomfort. The VAS consists of a line marked from 0 to 10, where 0 represents ‘completely relaxed’ and 10 represents ‘the greatest sense of unease, restlessness or discomfort you’ve ever felt’. Participants are asked to mark the point that best reflects how they feel at that moment. These physiological and subjective secondary measures aim to evaluate the emotional impact of the intervention. HRV and RR are recorded using the Hexoskin Pro vest (Hexoskin Inc., Montreal, Canada). Both variables are analysed during the baseline (t_1_) and experimental (t_2_) sessions. All participants complete the VAS at the end of both the baseline (t_1_) and experimental (t_2_) sessions, respectively.

All data are stored securely on UAH servers (institutional cloud storage with private folder accessible only to researchers; physical test data kept under lock/key in evaluation room). Data protection fully complies with EU GDPR (Regulation 2016/679) and Spanish LOPDGDD 3/2018: participant data dissociated via unique codes from outset, processed only with explicit consent within UAH’s educational/research framework, no transfers except as legally required, and all rights (access, rectification, deletion, etc.) exercisable via [contact]. Full details provided in Participant information sheet (Supplementary material S1 File). No cloud/edge computing or transmission to remote locations/outside EU occurs.

#### Intervention.

Images from the International Affective Picture System (IAPS) [34] are used during both the baseline (t_1_) and experimental (t_2_) sessions to expose participants to non-stressful and emotionally stressful stimuli, respectively. The IAPS is one of the most widely used standardised image sets for inducing emotions in experimental research. It has been shown to reliably elicit measurable changes across the three emotional response systems: subjective-verbal, behavioural and physiological [35]. For the baseline (t_1_), 40 low-arousal IAPS images have been selected, which collectively produce a mean arousal rating below 2.4 in both young and older adults, based on normative data from previous studies [36]. For the experimental session (t_2_), 40 high-arousal IAPS images were selected, collectively producing a mean arousal rating above 6.7 in both young and older adults [36].

Potential risks: no physical risks from assessments (supervised by trained professionals). High-arousal IAPS images may cause transient emotional discomfort, resolving shortly after exposure (“the sensation will pass shortly” -participant information sheet). Data security breach risk minimized through pseudonymization (unique codes from outset), local storage (UAH servers/OneDrive private folder, researcher access only; physical data under lock/key), and GDPR compliance (EU 2016/679, LOPDGDD 3/2018) – no identifiable personal data collected).

### Procedure

All study procedures are completed in a single laboratory visit. The study is conducted in the laboratories of the University of Alcalá (UAH), located in the Polytechnic Building and the Nursing and Physiotherapy Building. The researcher first provides verbal explanation of the study, answers all questions, and gives participants the information sheet (attached as Supplementary Information S1 File) to read, take home, and discuss with others as needed. Participants confirm understanding and sign the Informed Consent form only when ready. Firstly, participants read the information sheet and sign the Informed Consent form. Following this, baseline cognitive and physical assessments are carried out (Fig 2).

During the baseline test (t_1_) and the experimental test (t_2_), all participants perform the same tasks and wear both the Delsys Trigno system devices and the Hexoskin vest.

The baseline test (t_1_) is conducted first. Fixed order (low- then high-arousal) mimics real-life stress exposure patterns for ecological validity and avoids carryover effects from randomization. Participants are asked to sit on a stable chair and view low-arousal IAPS images for three minutes. After this period, a signal is given for them to begin the motor task test (gross motor, fine motor and balance tasks). This motor task test involves standing up from the chair, walking 2.3 metres over the pressure mat to a table, emptying the contents of one bottle (water) into another positioned on the table, turning around, walking back to the chair and sitting down again (Fig 3). Low-arousal IAPS images continue to be projected during the motor task test (Fig 2).

**Fig 3 pone.0341744.g003:**
[figure not shown]
Diagram of the area for carrying out motor tasks. By the authors.

Next, the experimental test (t_2_) is performed. With participants once again seated, they are asked to view high-arousal IAPS images for three minutes. After three minutes, they receive a signal to repeat the same motor task test (gross motor, fine motor and balance tasks) as in the baseline test (t_1_). During the execution of these motor tasks, high-arousal IAPS images continue to be projected (Fig 2).

Afterwards, the TUG and FRT are repeated. Finally, the Delsys Trigno system devices and the Hexoskin vest are removed.

### Signal pre-processing

The signals collected from the different sensors will undergo a preprocessing phase, which will include filtering, segmentation and extraction of relevant features. These steps will enable the removal of noise, identification of regions of interest and representation of the signals through meaningful attributes that reflect their dynamic behaviour. The extracted features will serve as the basis for subsequent analysis, aimed at maximising the useful information for classification and clustering tasks.

### Data modelling

One of the main objectives is to verify the potential of sensors to apply machine learning and data mining algorithms. Consequently, the primary outcome variables will be modelled.

Based on the extracted features, different modelling strategies will be explored using machine learning techniques, taking advantage of the functionalities offered by established programming libraries. These analyses will be primarily exploratory, aiming to identify informative patterns and assess the potential of different modelling approaches rather than to develop definitive predictive models. The workflow will follow standard best practices, including data preprocessing, feature scaling, and cross-validation to ensure model robustness and mitigate overfitting. Key performance metrics such as accuracy, precision, recall and F1-score, will be computed to evaluate each model’s performance objectively. To prevent data leakage, the dataset will be carefully partitioned into independent training and testing subsets, and transformations such as normalisation and dimensionality reduction, will be applied exclusively within the training pipeline. Overall, this framework supports a transparent and reproducible exploration of dimensionality reduction techniques, supervised and unsupervised learning methods to characterise participants’ behavioural patterns and overall condition.

### Statistical analysis

This study also establishes as main objectives the evaluation of postural control alterations under emotional stress in young and older adults (during both quiet standing and motor tasks), as well as determining whether these oscillations increase the risk of falls in the older population. To address these core aims, statistical analyses of the primary and secondary outcome variables will be performed using RStudio version 2024.09.0 (R Core Team).

Initially, a comprehensive descriptive analysis of the sample and the main variables will be carried out to establish their baseline characteristics and verify the quality of the data. Central tendency statistics (mean or median) and dispersion statistics (standard deviation and range) will be calculated for demographic variables. The distribution of the outcome variable data, including psychophysiological stress markers (HRV, RR, and VAS) and functional, biomechanical, and electromyographic metrics (muscle activity, ground pressure, acceleration and deceleration, TUG, and FRT) will be evaluated using the Shapiro-Wilk test to determine their normality. Variables that follow a normal distribution will be presented as mean ± standard deviation, while non-parametric variables will be described using the median and interquartile range. Finally, frequencies and percentages will be used to describe categorical variables.

Patterns of missing data will be examined prior to analysis. When missingness is minimal (e.g., < 5%), analyses will be conducted using complete cases. For variables with more substantial missingness, multiple imputation methods will be applied to reduce potential bias and maintain statistical power.

To assess whether the emotionally stressful stimulus produces psychophysiological effects in participants, secondary outcome variables will first be assessed: HRV, RR, and VAS of unease. Once the effect of stress has been verified, changes in the primary outcome variables will be evaluated: muscle activity (RMS y MDF), ground pressure, acceleration and deceleration, TUG, and FRT. All analyses will be conducted using mixed factorial ANOVAs, assessing the between-subjects factor GROUP (young, older adults) and the within-subjects factor TIMEPOINT (baseline, experimental). Type I error will be set at α = 5%, and partial eta squared (*η*_*p*_*²*) will be calculated as a measure of effect size. To control for multiplicity across the different outcome measures, p-values will be adjusted using the Benjamini–Hochberg procedure. Significant results will be subjected to Bonferroni-corrected post hoc *t*-tests, and Cohen’s *d* effect sizes will be calculated.

Additionally, subgroup analyses will be conducted within the older adult group, distinguishing between different levels of cognitive impairment and frailty status. The degree of cognitive impairment and frailty status will be determined based on the initial neuropsychological assessment. Correlational analyses between cognitive variables and physical test results will also be carried out.

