### Participants

Participants are divided into two groups: young adults (18–39 years) and older adults (≥65 years). Inclusion criteria are: age between 18–39 years for the young group or ≥65 years for the older group; ability to understand spoken and written Spanish sufficiently to follow the study information and instructions; corrected or uncorrected vision sufficient to view the image-based tasks; ability to walk safely over short distances in the laboratory setting, with or without usual assistive devices; and willingness to provide written informed consent. Participants are included if they wish to take part voluntarily and do not present any of the following exclusion criteria: illness, injury or previous trauma that contraindicates muscle exertion, balance exercises and/or walking; physical or mental illness that contraindicates exposure to emotionally stressful stimuli, such as severe depression or psychosis; or difficulty understanding the study information and signing the consent form.

To calculate the sample size, an a priori power analysis was performed. The significance level (α) was set at 0.05, with a statistical power (1 – β) of 0.80, assuming a medium effect size (f = 0.25) to detect the main interaction effect between the group factor (younger vs. older adults), and the stimulus factor (non-stressful vs. stressful) in the context of a 2x2 Mixed ANOVA (F-test, two tails). The selection of a medium effect size is justified because the induction of emotional stress causes a robust and quantifiable functional disruption in older adults’ balance reactions, which has been demonstrated in previous studies [12]. G*Power version 3.1.9.7 was used, and it was determined that the required sample size was 27 participants per group. Assuming a potential dropout rate of 10%, the minimum initial sample size is 30 participants for each group.

Young participants are recruited from various schools at the University of Alcalá (UAH), the Complutense University of Madrid (UCM) and other settings such as sports clubs or student associations. Older participants are recruited through contacts at the University for Older Adults at UAH, the Alcalá City Council, associations, residential centres and others.

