## Conclusion

DEPIE’s comprehensive multi-sensor approach (EMG from 7 muscles, pressure mapping, IMUs, HRV/RR) and standardized IAPS stress induction will establish whether acute emotional stress triggers detectable neuromuscular changes affecting postural control, providing foundational data for technology-assisted fall risk assessment systems. This would facilitate early support, promote self-awareness and aid in stress management. The integration of different technologies into the tests conducted during the study will improve the objectivity and accuracy of the assessment. The large-scale acquisition, analysis and processing of data will enable the practical application of the results by a range of professionals in the health and social sciences, not only those working with older adults, but also with people of all ages, as a comprehensive methodology is proposed for the evaluation of balance, fine motor and gross motor tasks. For all these reasons, the development of the DEPIE project will represent a significant contribution to the state of the art.

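### Cohen's d appears to be calculated only after a significant ANOVA, so the reported d values overstate small-to-moderate effects

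*Protocol article*

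**What the plan says.** The Statistical analysis section plans a mixed factorial ANOVA (GROUP by TIMEPOINT) for every primary and secondary outcome. The overall effect size carries no significance condition: "Type I error will be set at α = 5%, and partial eta squared" will be calculated. P-values are adjusted across outcomes by Benjamini–Hochberg. Then: "Significant results will be subjected to Bonferroni-corrected post hoc" *t*-tests, and the same sentence adds Cohen's d. The text does not state that d is withheld elsewhere, but it mentions d nowhere else.

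The same section plans descriptive summaries of the outcome variables (mean and SD, or median and IQR), also without a significance condition.

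The specific objectives in the Introduction are estimation aims: to measure, describe and compare the changes in balance and muscle activation in both age groups. The Conclusion presents the study as "providing foundational data for technology-assisted fall risk assessment systems".

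**The concern.** An estimate that is reported only when its test succeeds is conditioned on having come out large. With about 30 people per group, a small or moderate true change often fails the test. The changes that pass are, on average, those that chance pushed upward. Averaged over the d values that get reported, the effect is then too large, and more so the smaller the true effect.

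The study has many outcomes. EMG alone covers seven muscles on both sides, with RMS and median frequency named for analysis. That is 7 × 2 × 2 = 28 series if each is analysed separately (an assumption). Readers who compare sensors, or who size a later study, will naturally look at d because it is the standardised contrast. If d exists only for the successes, it misleads on size, and the outcomes that did not pass have no comparable signed estimate beside it.

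**Working it through.** **Inputs.** The Participants section plans for 80% power at the 5% level, with f = 0.25 for the interaction of group and stimulus, and reports that "it was determined that the required sample size was 27 participants per group". The dropout step reproduces: 27 / 0.9 = 30 per group. The selection rule comes from the Statistical analysis section. The true effects (0.3, 0.5, 0.8) are assumptions that span a range; the article gives none for d.

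**The planning effect on the d scale.** For the interaction, λ = f² × N × 2 / (1 − ρ), and on change scores λ = (n/2) d². The correlation ρ is not stated. With N = 54, n = 27 and ρ = 0.2, λ = 0.0625 × 54 × 2 / 0.8 = 8.44 and d = √(2 × 8.44 / 27) = 0.79. Power there is 0.81, which is consistent with the stated 27 per group. At ρ = 0.5, N = 34 would be enough. A d of about 0.8 is therefore a fair stand-in for the planned effect, and 0.3 and 0.5 stand for outcomes that respond less.

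**Model of the selection.** Let δ be the true older-group change in SD units, with 30 per group and 58 error df. The critical |t| is 2.00. The signal in the ANOVA test is:
- both groups change by δ, TIMEPOINT effect: λₜ = δ√60 = 7.75δ
- only older adults change, TIMEPOINT or interaction: λₜ = δ√15 = 3.87δ

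The older-group mean correlates 1/√2 with either test statistic and has standard error 1/√30. With a = 2.00 − λₜ, the mean reported d is approximately

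[δ + (1/√60) × φ(a) / (1 − Φ(a))] / J, where J = 1 − 3/(4 × 29 − 1) = 0.974 is the usual small-sample factor.

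**Worked case, δ = 0.3.**
- Both groups respond: λₜ = 2.32, a = −0.32, ratio = 0.379 / 0.626 = 0.605. Mean d = (0.3 + 0.129 × 0.605) / 0.974 = 0.39.
- Only older adults respond: λₜ = 1.16, a = 0.84, ratio = 0.280 / 0.200 = 1.40. Mean d = (0.3 + 0.129 × 1.40) / 0.974 = 0.49.

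Simulation of the ANOVA selection agrees with the formula:

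| True change, older adults | Both groups respond | Only older adults respond |
|---|---|---|
| 0.3 | 0.39 (1.3 times) | 0.49 to 0.50 (about 1.65 times) |
| 0.5 | 0.52 (1.05 times) | 0.63 (about 1.25 times) |
| 0.8 | under 10% inflation | under 10% inflation |

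Without any selection, mean d is 0.31, 0.51 and 0.82, because of the small-sample factor alone. Where both groups respond and δ is 0.5 or more, selection therefore adds almost nothing.

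**Between-group difference in change.** If a d is given for this contrast after a significant interaction (N = 60), the simulated means are 0.3 → 0.67, 0.5 → 0.73 and 0.8 → 0.88. The chances of passing are 21%, 48% and 86%. The smallest d that can pass is 2.00 × √(2/30) = 0.52, so a true 0.3 can never be reported near its value.

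**Partial eta squared.** With no true effect its mean is 1/(1 + df): 1/59 = 0.017 for 60 participants and 1/53 = 0.019 for 54. Across true values up to 0.138 the upward bias at N = 60 is 0.013 to 0.017.

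**The case against.** The strongest objection is that the plan already supplies effect information free of selection. Partial eta squared is planned for every ANOVA, descriptive summaries are planned for every outcome, and the Abstract promises open data. This stands against two stronger readings. A reader might infer that all reported effects are systematically too large. The article does not support that: selection touches d only, and the bias of partial eta squared is a separate mechanism worth less than 0.02. A reader might also infer that outcomes failing the test go without any estimate. The planned descriptives contradict that, although the article does not spell out a breakdown by group and timepoint or a summary of the change itself.

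It is also true that the restriction of d to significant results is inferred from the sentence rather than worded there. Partial eta squared is a conventional choice, and preferring omega squared is a matter of estimator taste, not an error. Confidence intervals and table layout are commonly left to an analysis plan, so their absence here is no finding in itself. Finally, near the planned effect the inflation is slight.

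What these points leave is the rule that the article does state. Partial eta squared cannot stand in for d: it does not show whether sway or muscle activity rose or fell, nor by how much older adults changed. The objectives ask for exactly those quantities in both groups.

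**Conclusion.** The point holds as a reporting defect of limited size. On the natural reading of the sentence, Cohen's d is conditional on a significant ANOVA. It then overstates a true older-group change of 0.3 by about 1.3 to 1.65 times (mean 0.39 to 0.50) and a true 0.5 by about 1.05 to 1.25 times (0.52 to 0.63). At 0.8 the overstatement is under about 10%.

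The figures assume 30 analysed per group, normal change scores with equal variance in the two groups, and selection at unadjusted p < 0.05. Benjamini–Hochberg makes the selection stricter, so the true inflation would be somewhat larger. The hypothesis tests, the error control and the sample size are not affected.

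**What to change.** State that for every prespecified primary and secondary outcome, whatever its p-value, the report will give:
- the t2 minus t1 change in each group (post minus pre for TUG and FRT), and
- the between-group difference in that change,

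each with a 95% confidence interval, in original units and as a standardised value (d or Hedges' g; the latter removes the small-sample excess). Keep the significance condition for the post hoc *t*-tests only, and word the sentence so that d is no longer tied to it. Partial eta squared may stay; adding omega squared is optional.

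The cost is a longer results table and less striking effect sizes. No new data, participants or tests are needed. The article gives recruitment as ongoing until July 2026, so the change can be fixed before results are known.
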